#### Hypothesis 1 – Behavioral Activation

To test for differences between the Imagery BA condition and the wait-list control condition in change in behavioral activation across the five measurement points (Sessions 1–4, follow-up), we plan to conduct a repeated-measures ANOVA on the BADS score with condition (Imagery BA vs. wait-list control) as between-subject factor and time (Sessions 1–4, follow-up) as within-subject factor in an intention-to-treat analysis.

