The present study will test the acceptability, feasibility, and effects of a 4-session imagery BA intervention delivered over the internet on behavioral activation and depressive symptoms in individuals meeting diagnostic criteria for MDD. While results from several studies have already supported the use of BA in online settings (e.g., Mueller-Weinitschke et al., 2023; Potsch & Rief, 2024; Puspitasari et al., 2017; Weitzel et al., 2022), the presented study will be the first to test the acceptability, feasibility, and effects of an imagery-enhanced BA intervention in an online setting. Besides, the present study will include multiple measurements of potential mechanisms of change, thereby providing insights into the relationship between the procedure (imagery-enhanced activity scheduling), potential mechanisms of change (reward anticipation, motivation, and behavioral activation), and outcome (depressive symptoms). In addition, the present study will explore the moderating effects of imagery ability, anhedonia, and avoidance tendencies.

Specifically, we expect to find (1) an increase in behavioral activation, measured with the Behavioral Activation for Depression Scale (BADS; Kanter et al., 2007) weekly from baseline to Session 4 and at two-week follow-up, and (2) a decrease in depressive symptoms, measured with the Beck Depression Inventory-II (BDI-II; Beck et al., 1996) at baseline, Session 4, and at two-week follow-up, for participants in the Imagery BA condition, compared to participants in the wait-list control condition. We expect that this difference between conditions in behavioral activation and depressive symptoms will be present at the end of the intervention (Session 4) and will be maintained at two-week follow-up.

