## Method

### Design

The study is a two-arm randomized controlled trial with one active intervention condition (Imagery BA) and one wait-list control condition. Participants in both conditions are invited to complete questionnaires at baseline (Session 1), Weeks 1-3 after baseline (Sessions 2-4) and at follow-up (Week 5 after baseline). The study has been pre-registered (see Heise et al., 2022S).

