### Statistical Analyses

We will regard *p*-values less than .05 as criteria for statistically significant results. All reported *p*-values will be two-tailed.

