#### Hypothesis 2 – Depressive Symptoms

To test for differences between the Imagery BA condition and the wait-list control condition in change in depressive symptoms across the three measurement points (Session 1, Session 4, follow-up), we plan to conduct a repeated-measures ANOVA on the BDI-II score with condition (Imagery BA vs. wait-list control) as between-subject factor and time (Session 1, Session 4, follow-up) as within-subject factor in an intention-to-treat analysis.

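### The overall condition-by-time ANOVA cannot show whether a difference is present at Session 4 and maintained at follow-up; name contrasts at those two times

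*Protocol article*

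**What the plan says.** The hypotheses stand at the end of the introduction of the protocol article, just before Method. They have two layers. The broad one is that behavioral activation rises and depressive symptoms fall in the Imagery BA condition relative to wait-list, over all the scheduled measurements. The specific one is that the difference "will be present at the end of the intervention (Session 4) and will be maintained at two-week follow-up".

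Under Statistical Analyses, each outcome has one confirmatory test. For BADS the ANOVA is meant "To test for differences between the Imagery BA condition and the wait-list control condition in change in behavioral activation across the five measurement points", with "time (Sessions 1–4, follow-up) as within-subject factor in an intention-to-treat analysis". For BDI-II it looks for differences "in change in depressive symptoms across the three measurement points", with "time (Session 1, Session 4, follow-up) as within-subject factor in an intention-to-treat analysis". Session 1 is the baseline according to Design ("Participants in both conditions are invited to complete questionnaires at baseline (Session 1), Weeks 1-3 after baseline (Sessions 2-4) and at follow-up"), so the baseline score enters as a level of the outcome. The decision rule is general: "We will regard *p*-values less than .05 as criteria for statistically significant results", and "All reported *p*-values will be two-tailed".

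Neither analysis paragraph names a contrast at Session 4 or at follow-up, or says what result would count as maintained. The Exploratory Analyses section adds none.

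**The concern.** Because the ANOVAs are worded in terms of change, the test that matters is the condition x time interaction. It has 4 degrees of freedom for BADS (five time points) and 2 for BDI-II (three). Such a test asks whether the difference between arms varies over time in any way. It does not ask when the difference exists or in which direction.

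The article's specific expectation concerns two named times. If the overall test is significant, that expectation still has no pre-specified test. An early difference that has gone by Session 4, or one that is gone by follow-up, can produce the same significant result as the expected pattern. Whoever writes the report must then choose follow-up comparisons after seeing the means, and that choice decides whether the trial claims a lasting effect.

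**Working it through.** **Inputs.** From the document: 140 complete observations (Participants, sample size paragraph), 1:1 allocation (70 per arm), two-sided 0.05, five time points for BADS and three for BDI-II. The article gives no numeric effect size, SD or correlation between time points, so these are assumptions: a difference of d = 0.4 SD where an effect exists, equal correlations r between all time points, and r from 0.5 to 0.8. The plan has no figure of its own on this point to reproduce; 140 is taken as given.

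**Overall test.** With delta_t the arm difference in SD units at time t, the noncentrality is lambda = (N/4) x sum of (delta_t - mean delta)^2 / (1 - r). The degrees of freedom are m - 1 and (N - 2)(m - 1): 4 and 552 for BADS, 2 and 276 for BDI-II.

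**Can it tell the BDI-II patterns apart?** For a sustained effect (0, 0.4, 0.4) the mean is 0.267 and the sum of squares is 0.1067. For an effect lost by follow-up (0, 0.4, 0), and for one seen only at follow-up (0, 0, 0.4), the mean is 0.133 and the sum of squares is again 0.1067. At r = 0.5, lambda = 35 x 0.1067 / 0.5 = 7.47 and power is 0.68 for all three. The equality holds for any d and any common r, because the sums of squares are identical.

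**BADS, effect at Sessions 2-3 only** (0, 0.4, 0.4, 0, 0). The mean is 0.16 and the sum of squares is 3 x 0.0256 + 2 x 0.0576 = 0.192. At r = 0.5, lambda = 35 x 0.192 / 0.5 = 13.44. Power is 0.85, 0.92 and 0.98 at r = 0.5, 0.6 and 0.7, although the true difference is zero at both times named in the hypothesis.

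**BADS, linear rise kept or lost.** (0, 1/3, 2/3, 1, 1) x 0.4 and (0, 1/3, 2/3, 1, 0) x 0.4 both have sum of squares 0.121 and power 0.63 at r = 0.5.

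**Role of baseline.** The Session 4 contrast has residual variance proportional to 2(1 - r) as a change score and 1 - r^2 when adjusted for baseline. The ratio is (1 + r)/2, that is 0.75, 0.80, 0.85 and 0.90 at r = 0.5, 0.6, 0.7 and 0.8. Adjustment therefore lowers the variance by 25% to 10%.

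**Power for a real, sustained d = 0.4:**

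| Test | r = 0.5 | r = 0.7 | r = 0.8 |
|---|---|---|---|
| Overall, BADS, linear rise | 0.63 | 0.87 | 0.97 |
| Overall, BADS, no effect at Session 2 (0, 0, 2/3, 1, 1) | 0.78 | 0.95 | above 0.99 |
| Overall, BDI-II | 0.68 | 0.89 | 0.98 |
| Baseline-adjusted Session 4 contrast | 0.77 | 0.91 | 0.97 |

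**Both gated tests together.** At r = 0.5 each adjusted contrast has noncentrality 0.4 / sqrt(0.75) x sqrt(35) = 2.73. The two are correlated (r - r^2)/(1 - r^2) = 0.33. The probability that both are significant is about 0.64 (normal approximation).

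**The case against.** The strongest reply is that the ANOVA does answer the broad hypothesis. More improvement in one arm over the scheduled measurements is what a condition x time test addresses, and the sentence on Session 4 and follow-up is a further expectation about the shape of the effect. That stands. A reader might infer that the planned analysis fails to test the hypothesis at all; the introduction and the analysis paragraphs do not support that.

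Second, this is a condensed article that refers to a pre-registration not shown here. Contrasts after a significant interaction may be set out there, and nothing says that the interaction p-value alone will be read as proof of maintenance. This also stands as a limit. It does not remove the point, because the article does fix a confirmatory test under each hypothesis, and that test cannot decide the specific expectation.

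Three stronger readings are tempting and should not be drawn:

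- That the baseline score is wasted. The interaction uses it as the within-person reference, and the test is valid under randomization. The cost is one of efficiency.
- That Session 2 dilutes the BADS test because it comes before the imagery task. With no effect at Session 2, overall power rises (0.78 against 0.63 at r = 0.5), since Session 2 then acts like a second baseline. The active arm has also had psychoeducation and activity monitoring by then, so an effect at Session 2 is possible.
- That the overall test loses power in general. The table shows a loss at r = 0.5 for some profiles, none by r = 0.8, and a reversal when Session 2 carries no effect.

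**Conclusion.** The point holds as a mismatch between one stated expectation and the test listed for it. A significant overall interaction supports differential change. It does not support a difference at Session 4 that lasts to follow-up. For BDI-II the test gives the same power to the expected pattern and to two patterns that contradict it. For BADS an effect absent at both named times is significant in 85 to 98% of trials.

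The percentages rest on N = 140, d = 0.4, r = 0.5 to 0.7 and equal correlations. The exact equality of the BDI-II patterns needs only the equal correlations. That an overall test does not locate a difference needs no assumption.

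The case for change rests on matching the test to the claim, with a modest gain in precision from baseline adjustment. It does not rest on a promise of more power, which depends on a correlation and an effect profile that the document does not give. The change should be made; the planned ANOVA is not invalid.

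**What to change.** For each outcome, state in the analysis section:

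1. The primary contrast is the arm difference at Session 4, adjusted for the Session 1 score, from a repeated-measures model of the post-baseline scores.
2. The baseline-adjusted difference at follow-up is tested only if the Session 4 contrast is significant. Maintained means that this second test is significant in the same direction.
3. Both differences are reported with 95% confidence intervals.
4. The overall condition x time interaction is kept as supportive.

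This is analysis wording only, with no new data, visits or participants. The costs are a deviation note against the pre-registration (unless it already names these contrasts), secondary status for BADS effects confined to Sessions 2-3, and a more demanding claim. At d = 0.4 and r = 0.5, the chance of passing both gated tests is about 64%, close to the overall test's 63% (BADS, linear rise) and slightly below its 68% (BDI-II).

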#### Hypothesis 2 – Depressive Symptoms

To test for differences between the Imagery BA condition and the wait-list control condition in change in depressive symptoms across the three measurement points (Session 1, Session 4, follow-up), we plan to conduct a repeated-measures ANOVA on the BDI-II score with condition (Imagery BA vs. wait-list control) as between-subject factor and time (Session 1, Session 4, follow-up) as within-subject factor in an intention-to-treat analysis.

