### Participants

Inclusion criteria are (a) meeting the diagnostic criteria for a current major depressive disorder (MDD) as indicated by the Diagnostic Short-Interview for Mental Disorders (Mini-DIPS; Margraf et al., 2017), (b) a BDI-II score ≥ 14, indicating at least mild levels of depression, and (c) age between 18 and 65 years. Participants will be excluded if (1) they are currently in treatment for a mental health condition (psychotherapy and/or medication), (2) they present high levels of suicidality (as indicated by answers > 1 for item 9 of the BDI-II or the respective section in the Mini-DIPS), or (3) if they are meeting diagnostic criteria for one or more of the following disorders: bipolar disorder, psychotic disorders, or substance dependence.

*Sample Size.* Our aim is to obtain a dataset containing *n* = 140 complete observations, that is, with measurements for all four sessions and follow-up. This sample size was pre-registered (Heise et al., 2022S) and determined a priori using GPower (Faul et al., 2009). We assumed a small effect size (as observed in initial pilot testing), 95% Power, and α = 0.05. To account for attrition as observed in initial pilot testing, in which approximately 26% of baseline participants did not complete the follow-up assessment, we plan to recruit a total of *N* = 192 participants from the general population.

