### Procedure

#### Screening Process

To inform potential participants about the present study, advertisements and leaflets will be distributed through various online (social media groups, forums focusing on depression) and offline (general practitioners, psychotherapists, psychiatrists, outpatient clinics, university student counseling services) channels. Anyone interested in the study will be referred to an online screening website, where detailed information about the study’s procedures are provided and informed consent is obtained from interested potential participants. Next, participants complete the BDI-II and screening questions for the Mini-DIPS. If complying with inclusion and exclusion criteria, participants may book an appointment for a telephone interview by choosing a suitable date/time from a list displayed online.

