#### Randomization and Recruitment Stop

Block randomization will be used, where each participant will be randomly assigned to one of two equally sized, predetermined blocks. Randomization is performed using the respective function provided by the survey platform formr (Arslan et al., 2020) used in this online study. Recruitment will stop if either of the following two criteria is met: (a) The number of recruited participants, i.e. participants who have completed at least the baseline questionnaires and have been randomized, has reached *N* = 192 or (b) the number of complete observations, i.e. datasets containing measurements for all four sessions and follow-up, has reached *N* = 140. As a compensation for taking part in the study, participants will receive a 25 € online retailer voucher.

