##### Depressive Symptoms

Depressive symptoms will be assessed at baseline (Session 1), Session 4, and at two-week follow-up using the Beck Depression Inventory-II (BDI-II; Beck et al., 1996). The BDI-II measures depressive symptom severity across 21 symptoms by letting respondents choose from four (for two symptoms, seven) statements (e.g., “I blame myself all the time for my faults.”) ranked by increasing severity (scoring 0-3 points per symptom). Total scores can range from 0 to 63, with 0-13 indicating minimal depression, 14-19 mild depression, 20-28 moderate depression, and 29-63 severe depression. Reliability and validity of the BDI-II are well supported (Kühner et al., 2007; Wang & Gorenstein, 2013).

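### The BDI-II is measured at screening and at Session 1, but the primary model treats Session 1 as an outcome level and leaves the screening score out, giving up some precision

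*Protocol article*

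**What the plan says.** The Screening Process section puts a BDI-II on the screening website, ahead of the telephone interview: "Next, participants complete the BDI-II and screening questions for the Mini-DIPS". Table 1 marks the BDI-II at screening as well as at Session 1, Session 4 and follow-up. As an outcome, however, it is defined from Session 1 onwards: "Depressive symptoms will be assessed at baseline (Session 1), Session 4, and at two-week follow-up".

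The only use described for the BDI-II at entry is eligibility, through item 9 and the criterion of "a BDI-II score ≥ 14, indicating at least mild levels of depression". Randomization and Recruitment Stop counts as recruited those "participants who have completed at least the baseline questionnaires and have been randomized", which implies that the Session 1 questionnaires come before allocation.

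The Hypothesis 2 model is a "repeated-measures ANOVA on the BDI-II score with condition (Imagery BA vs. wait-list control) as between-subject factor and time (Session 1, Session 4, follow-up", with time as the within-subject factor and analysis by intention to treat. It names no covariate. The Exploratory Analyses section does not use the screening score either.

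**The concern.** A single BDI-II score carries measurement error and day-to-day variation. A second score on the same scale, taken before randomisation, can remove some of that noise from the treatment comparison, and adjusting for a pre-randomisation value does not bias a randomised contrast. The score should already exist for every randomised participant, because entry depends on it.

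The plan expects only a small effect on a primary outcome, so unexplained variance in the BDI-II contrast matters. The article states the model type, both factors and every time level. The comment therefore addresses a stated choice and does not complain of detail left to a fuller plan.

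**Working it through.** **Order of measurement.** Screening BDI-II, telephone interview, Session 1 BDI-II, randomisation, Session 4, follow-up. The place of Session 1 before randomisation is inferred from the definition of a recruited participant; Figure 1 is not available to confirm it.

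**The plan's own figures.** The article gives no BDI-II standard deviation or correlation, so it has no precision figure to reproduce. The attrition step gives 140/(1 − 0.26) = 189.2, so 190, close to the stated 192. The 140 can be neither confirmed nor refuted, because the numerical effect size, the correlation and the number of measurements are not stated. For an interaction test at correlation .5, f = 0.125 with four measurements needs 140, while f = 0.10 with three needs 260. Nothing below depends on this.

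**Formulas.** Take unit variance at each occasion. Let r1 be the correlation of Session 1 with a post-treatment score, r0 that of screening with the post-treatment score, and rb that of screening with Session 1. All three are assumptions. Residual variance of the treatment contrast for one post-treatment score:

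- Planned change contrast: Vc = 2(1 − r1)
- Session 1 as covariate: V1 = 1 − r1²
- Session 1 and screening as covariates: V2 = 1 − (r1² + r0² − 2·r1·r0·rb)/(1 − rb²)
- Proportional cut from adding screening only, as a covariate to the change contrast: (r0 − rb)²/[2(1 − r1)]

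For r1 = .6, r0 = .5, rb = .7: V2 = 1 − (.36 + .25 − .42)/.51 = 1 − .373 = .627, and V2/V1 = .627/.640 = .980.

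| r1 / r0 / rb | Vc | V1 | V2 | V2/V1 | Equivalent extra participants on 192 | Cut, Vc to V1 | Cut, Vc to V2 | Screening added to change contrast only |
|---|---|---|---|---|---|---|---|---|
| .6 / .5 / .7 | .800 | .640 | .627 | .980 | about 4 | 20% | 22% | 5.0% |
| .5 / .45 / .7 | 1.000 | .750 | .730 | .974 | about 5 | 25% | 27% | 6.3% |
| .6 / .6 / .7 | .800 | .640 | .576 | .901 | about 21 | 20% | 28% | 1.25% |

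Extra participants are 192 × (V1/V2 − 1).

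**Two readings of the table.** First, beyond Session 1 adjustment, screening cuts variance by about 2% to 10%, while conditioning on Session 1 alone cuts 20% to 25%. Second, the form of adjustment matters. The setting with the largest gain as a second covariate (.6/.6/.7) gives only (.1)²/.8 = 1.25% if screening is added while Session 1 stays an outcome level. That gain is exactly zero whenever r0 = rb.

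**Sensitivity.**

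- *Equal correlation across all occasions.* V1 = 1 − ρ² and V2 = 1 − 2ρ²/(1 + ρ). The further cut from screening is 8% at ρ = .4, 11% at .5, 17% at .7 and 20% at .8.
- *Equal correlation with screening truncated at 14* (assumed SD 9, mean 18 to 26, ρ .5 to .8). The cut is 6% to 18%.
- *Correlation decaying with time, plus measurement error.* The cut is about 1% to 5%. Under pure first-order autoregressive decay it is 0%.

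**Effect on power and interval width.** The plan states "95% Power, and α = 0.05" and that its p-"values will be two-tailed", so the implied noncentrality is 1.960 + 1.645 = 3.605 (normal approximation). Dividing by √.980 gives 3.642 and power of about 95.4%. Dividing by √.901 gives 3.798 and about 96.7%. The confidence interval narrows by 1 − √.980 = 1% to 1 − √.901 = 5%.

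**The case against.** The strongest reply is that nothing here is an error. The condition-by-time ANOVA is valid without the screening score, many trials use such a score only for eligibility, and the size of the gain rests on correlations the documents do not give. From a stated 95% power, the improvement is at most a couple of percentage points. All of this stands, and it limits the point to one of efficiency.

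A second reply is that the benefit of screening cannot be separated from the handling of Session 1. This also stands. A reader might infer that adding one covariate to the planned ANOVA recovers the precision. The table shows otherwise: with Session 1 left as an outcome level, the gain can be 1.25% or zero. Truncation at the entry threshold does not bias a covariate, but it does lower its correlation with outcome and hence its benefit.

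A third reply is that covariates may be listed in a fuller plan. That has less force, because Hypothesis 2 fixes Session 1 as a level of the time factor, so the article has already made the choice that matters most.

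**Conclusion.** The point holds as a modest efficiency gain forgone on a primary outcome. Two BDI-II scores appear to precede randomisation. The stated model uses one as an outcome level and ignores the other. Beyond Session 1 adjustment, screening is worth about 2% to 10% of residual variance under the assumed correlations, and possibly near 0% if correlation decays quickly. Higher figures, up to 20%, require the older, truncated screening score to predict outcome as well as Session 1 does. The larger part of the gain over the planned contrast may come from conditioning on Session 1.

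A reader might go further and infer that the planned test is biased or that the trial is underpowered. The documents support neither. Randomisation protects the planned contrast, and the sample size cannot be checked from the inputs given. The conclusion also assumes that the Session 1 BDI-II is completed before allocation, which the article implies but does not spell out.

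**What to change.** In Hypothesis 2, make Session 4 and follow-up BDI-II the outcomes in a repeated-measures ANCOVA or mixed model with condition, time and condition-by-time. Include both the Session 1 and the screening BDI-II as covariates, each with its interaction with time. State that both scores are recorded before randomisation. Do not make screening an additional outcome time level: as the likely selection score it is subject to regression to the mean. Fix the wording before outcome data are examined.

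The cost is two covariates and their interactions with a two-level time factor, that is four parameters. No new data are needed and participants bear no extra burden. If screening turns out to add nothing beyond Session 1, only those few degrees of freedom are lost.
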